### Quality Control

Several procedures were employed to ensure the quality of the study data, thus maximizing the validity and reliability of the program delivery and outcome assessments. They were:

• An eight -hour training the professionals who participated in the study in motivational interviewing, pharmocological treatment of smoking, and use of the electronic data collection system.

• Use of an electronic data collection system with a system of warnings and intenal coherency noms.

• A full time person contracted to provide technical and methodological support to the study participants.

• Regular meetings and mailings between members of the study group and all participating centers.

### Ethical Aspects

In the first contact with the patient, he or she will be given information about the study and will sign an informed consent form if he or she wishes to participate. The informed consent will detail the ethical conditions and the paricipant's right to intimacy, anonymity, confidentiality, withdrawl and information. The researchers also commit to respect the norms of good clinical practice, as well as the requirements of the Helsinki Declaration. The protocol has been evaluated and approved by the Ethical Committee of Scientific Reseach and the Jordi Gol Center for Investigation in Primary Care. Confidentiality of data: Only the investigators and monitors/auditors of the study will have access to the data of the subjects who agreed to participate.

## Discussion

Although there are studies that use intensive interventions in smoking cessation such as the ISTAPS study [20], the majority are directed towards the general population. The challenge of the present study is to exclusively direct the intervention towards diabetic smokers in PC. The fact that these type of patients are resistant to change should not be an obstacle, as it is a priority to address the topic of smoking when dealing with patients with an elevated cardiovascular risk. Furthermore, it should be kept in mind that the intention of this intervention is not only to achieve continued smoking abstinence, but also to achieve partial goals, such as advancing in the stages of change of Prochaska and DiClemente and the reduction of the number of cigarettes smoked per day. These partial goals can motivate a healthcare professional who has tried unsuccessfully on several occasions to get his or her patient to quit smoking, to continue working towards progress.

One of the stengths of the ITADI study is the population of the study, diabetic patients that attend PC. Another strength is the design of the study, which is pragmatic in terms of time and material resources needed. If the hypothesis of the present study is confimed, it could be incorporated into current PC clinical practice guidelines. The large number of healthcare professionals and patients involved in the present study is another strength, as it reinforces the external validity of the data.

The randomization has been done by PCT and not by patient, so as to avoid the unethical situation in which a healthcare professional would feel obligated to use the motivational interview and pharmocotherapy in only some of his or her patients. This will also prevent contamination between healthcare professionals of the same center. Although the unit of randomization is the center, the intervention is given at the individual level and the outcomes are also measured at this level. The estimation of the design effect will be taken into account in all of the main analyses.

The motivational interview techiques require personal communication and empathy from the part of the healthcare professional towards his or her patient. The training sessions are one full day, although it is known that the more training the professional has in motivational interviewing, the more he or she is able to apply the learned skills [32].

Cooximetry is a technically simple and affordable method to apply in PC, as well as valid and useful [12]; however, it has some management limitations. In order to overcome these limitations, the healthcare professionals of both study groups will be trained in how to use cooximeters. Furthermore, an instruction manual and audiovisual guide will be designed on how to use the cooximeters. The cooximetry measures will be taken in the afternoon in homogenous and standarized conditions.

Finally, the current study will try to describe the profile of a diabetic smoker who receives the most benefit from an intensive smoking cessation intervention in PC. The goal is to use the results of the study as a foundation for a protocolized intervention in PC guidelines for diabetes

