**Discussion:**

The present study will try to describe the profile of a diabetic smoker who receives the most benefit from an intensive intervention in primary care. The results will be useful for primary care professionals in their usual clinical practice.

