### Sample size calculation

The sample size has been calcuated by multipying the size of a randomized simple design by the design effect. In the simple randomized design, considering an alpha error of 0.05 a beta error of 0.20 in a bilateral contrast, and given that 15% of diabetics are smokers, 124 subjects were needed in each study group in order to determine a difference in continued abstinence of greater than or equal to 12% between study groups. A continued abstinence of 5% was assumed for the non intervention group, and a potential loss of follow-up of 20% was estimated.

Using an intracluster correlation coefficient of 0.05 [28-30], and based on an average of 25 diabetic smokers per PCT, the design effect is 2.2. Therefore, 546 diabetic smokers and 22 PCT were needed. The sample size was calculated using the Granmo 5.2 program for Windows.

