### Statistical analysis

Data will be analyzed in concordance with the Consort Cluster guide [31], and all analyses will be done on an intention to treat basis. A descriptive analysis and an analysis of baseline comparability between the study groups will be performed for the variables studied. A T-student test or a U Mann Whitey will be used to compare means with two categories, an ANOVA test will be done to compare means with two or more categories, and a Chi- squared test or a Chi -squared tendency test will be done to compare categorical variables. A multilevel logistic regression and a Poisson regression will be done to evaluate the association between each of the dependent variables and the independent variables that have resulted statistically significant in the bivariate analisis. All analisis will be adjusted for potential confounding factors and for variables with clinical relevance. All tests will be done with a 95% bilateral confidence interval. SPSS 15, STATA 10 and HLM6 will be used.

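### The stated aim of profiling the smoker who benefits most is not answered by the stated regressions, whose bivariate entry rule can discard a true effect modifier

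*Protocol article*

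**What the plan says.** The closing paragraph of the Discussion gives this as something the study will attempt: to "describe the profile of a diabetic smoker who receives the most benefit from an intensive smoking cessation intervention in PC". In the Abstract, its Discussion paragraph has the same aim: "The present study will try to describe the profile of a diabetic smoker who receives the most benefit from an intensive intervention in primary care".

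This aim is neither the principal objective nor one of the three secondary objectives. The Hypothesis and the Sample size calculation concern only the overall 12-point difference in continued abstinence.

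Under Statistical analysis, after descriptive and bivariate tests, multilevel logistic and Poisson regressions are planned "to evaluate the association between each of the dependent variables and the independent variables". Entry is restricted to those "independent variables that have resulted statistically significant in the bivariate analisis". The section adds: "All analisis will be adjusted for potential confounding factors and for variables with clinical relevance". The article nowhere mentions an interaction with study group, a subgroup contrast or any other analysis of effect modification. The list of independent variables does not name study group, and the article does not say how it enters these models.

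**The concern.** Benefit from an intervention is the IG-NIG contrast. To say who benefits most, that contrast has to be compared across types of patient. A regression of abstinence on patient characteristics answers a different question: which characteristics go with abstinence.

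The two questions can have different answers. A characteristic may predict quitting equally in both arms and say nothing about who gains from the intervention. A characteristic may also change the effect strongly and yet show no overall association with abstinence. The entry rule makes the second case worse, because such a variable is removed before the regression is fitted.

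At stake is how a descriptive claim in the report is read. If factors associated with abstinence are presented as the profile of those who benefit most, clinicians could direct an intensive intervention by the wrong characteristics.

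**Working it through.** **1. The plan's own figure.** Sample size calculation: 5% versus 17% (5% plus 12 points), "considering an alpha error of 0.05 a beta error of 0.20 in a bilateral contrast", 20% loss.
- The arcsine formula for two proportions gives 99 per group; 99 / 0.80 = 124, as stated.
- Design effect: 1 + (25 − 1) × 0.05 = 2.2, as stated.
- Total: 2 × 124 × 2.2 = 545.6, so 546; 546 / 25 = 21.8, so 22 teams, as stated.

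The size for the overall comparison reproduces. It was not set for a comparison of effects between types of patient.

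**2. Can the screen lose a true modifier?** Assumed rates, two equal strata, 1:1 allocation, chosen so that the arm averages match the plan:

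| Stratum | NIG | IG | Benefit | Pooled abstinence |
|---|---|---|---|---|
| Factor present | 2% | 20% | 18 points | (2 + 20)/2 = 11% |
| Factor absent | 8% | 14% | 6 points | (8 + 14)/2 = 11% |
| Average | 5% | 17% | 12 points | 11% |

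The factor has no bivariate association with abstinence, so apart from chance the screen drops it. If it is kept as an adjustment variable, a logistic model with study group and the factor but no product term gives it an odds ratio of 1.00. The modification is not an artefact of scale: the IG/NIG odds ratio is (0.20/0.80)/(0.02/0.98) = 12.3 with the factor and (0.14/0.86)/(0.08/0.92) = 1.9 without it.

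**3. Can the regression name a factor that does not mark greater benefit?** Assumed rates again, with the same arm averages:

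| Stratum | NIG | IG | Benefit | Pooled abstinence |
|---|---|---|---|---|
| Factor present | 8% | 20% | 12 points | 14% |
| Factor absent | 2% | 14% | 12 points | 8% |

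The model without a product term gives the factor an odds ratio of 1.92 (p = 0.024 with 546 patients, ignoring clustering and loss). The factor would be reported as important although the absolute benefit is the same in both strata.

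**4. What precision would an interaction have?** Assumptions: a patient-level factor split 50/50, and 5% and 17% in both strata for the variance.
- Analysed per arm: 546 / 2 × 0.80 = 218.
- Variance term: 0.05 × 0.95 + 0.17 × 0.83 = 0.0475 + 0.1411 = 0.1886.
- SE of the difference between two stratum-specific risk differences: 2 × √(0.1886 × k / 218), where k is the variance factor for clustering.
- Factor balanced within centres, k = 1 − 0.05 = 0.95: SE = 0.057. Detectable with 80% power: (1.96 + 0.84) × 0.057 = 0.16, or 16 points.
- Full design effect, k = 2.2: SE = 0.087. Detectable: 2.8 × 0.087 = 0.24, or 24 points.

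Power can be lower on the logit scale. With a control rate of 5% in both halves, benefits of 18 versus 6 points and 437 analysed, power is 54% on the risk-difference scale and 23% on the logit scale with no design effect. With the full 2.2 it is 29% and 13%.

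**The case against.** The strongest reply is that this is an article, that the aim is modest, and that interaction terms for an exploratory question belong in a fuller plan. Much of that stands. The wording is only that the study will try; the aim is not a listed objective; the article neither describes its models as main-effects only nor rules out product terms. A reader might infer that the trial commits itself to the profile, or that the plan pools the arms and excludes interactions. The text supports neither reading.

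What the reply does not cover is the entry rule. The article does more than omit detail: it fixes a screen on bivariate significance, and that screen selects on association with the outcome. A fuller plan that followed it would carry the same problem. The clause on clinically relevant variables may keep a characteristic in the model, but as an adjustment term.

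A second reply is that a logistic model with one common odds ratio does imply absolute benefits that differ with baseline risk. That is true. At the odds ratio implied by 5% versus 17% (about 3.9), a control rate of 2% implies a benefit of about 5 points and one of 10% about 20 points. But the model imposes this pattern and does not test it.

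A reader might also infer that the reported profile would turn out to be the reverse of the truth, or that guideline content would rest on it. Neither is supported. The examples use assumed rates and show what can happen, not what is likely. The Discussion ties guideline use to confirmation of the main hypothesis and to the study results in general, not to the profile.

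**Conclusion.** The mismatch holds. The aim concerns effect modification, while the stated method identifies factors associated with abstinence and selects them by a rule that can discard a true modifier. In an example consistent with the plan's 5% and 17%, a factor separating an 18-point from a 6-point benefit would be lost at the screen. That example rests on assumed stratum rates and equal strata.

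The consequence is limited to a hedged, additional aim. The primary comparison and its sample size are untouched. Even with the right model the trial could show only large differences in benefit, about 16 to 24 points under the assumptions in the working, so any profile would have to be called exploratory.

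**What to change.** Choose one of two changes.

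1. Keep the aim and give it its own analysis. Name a short fixed list of baseline variables that are already collected (stage of change, nicotine dependence, motivation, diabetes type, sex) and exempt them from the bivariate screen. Fit the interaction of study group with each in the multilevel model. Report the IG-NIG difference with its 95% CI in each level, say on which scale the interaction is assessed, and label the whole analysis exploratory.
2. Reword the aim, in both the Abstract and the Discussion, to factors associated with abstinence. The stated regressions then match the claim.

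The first costs a few extra models on data already collected, and its drawback is wide intervals. The second costs only a change of wording, but gives up the question of who benefits most. Restricting the regression to the intervention group is no substitute, since that still shows who quits and not who benefits.
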